The focus for assessing the relative effect of the PA intervention on cognition is based on two secondary cognitive outcomes: the Digit Symbol Substitution Test (DSST) and the Hopkins Verbal Learning Test (HVLT). Each will be tested at the 2-sided  $\alpha=0.05$  level. LIFE-P results, and data from other cognitive trials we have conducted (e.g. WHISCA, CoSTAR, GEMS), indicate that longitudinal correlations of these measures are likely to range from  $r=0.50$  to  $r=0.70$  over 4 yrs. In GEMS, at 4 yrs 92% of all expected face-to-face cognitive assessments (3MSE, CDR and ADAS-COG) were completed in a population of adults age  $\geq 75$  years (mean 79 years). In LIFE-P, retention was very strong at 12 months. Meta-analyses report that measures of executive function on average are relatively improved by 0.3 standard deviations (SD) by aerobic exercise interventions. Since most trials contributing to these meta-analyses were conducted in more healthy cohorts and are of shorter duration than LIFE, we anticipate that the effect size in LIFE will be less: we target an average effect size of half of this (e.g. 0.15 SD). We project from LIFE-P that this translates to average effects of 1.8 (DSST; and 0.8 (HVLT) units. Data

from the Women's Health Initiative Memory Study (WHIMS) indicate that annual assessments are not optimum in many cognitive trials, thus we will collect data only at baseline and year 2 (and assume an 8%/yr accumulating lost follow-up). Standard power calculations (i.e. a covariate-adjusted z-test with Bonferroni critical value of 1.96) provide the powers listed in Table 3.3.2 associated with drop-in/drop-out rates of 0%, 10% and 20% for both arms and exam times (i.e., reducing the difference between arms by these amounts).

| Table 3.3.2              | Projected Power: N=1,600 Enrolled                              |     |     |
|--------------------------|----------------------------------------------------------------|-----|-----|
|                          | Cross-Over Rates (applied equally to both arms and exam times) |     |     |
| Longitudinal Correlation | 0%                                                             | 10% | 20% |
| 0.50                     | 89%                                                            | 82% | 72% |

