##### **4.1.2. Establishing Eligibility**

Eligibility is established in a multi-step screening process. The first step is a telephone screen to assess specific inclusion and exclusion criteria. This is followed by an interviewer assessment, including the administration of the SPPB, the 400 meter walk test, the Modified Mini-Mental State (3MSE) exam and an interview. Finally, the potential participant receives an examination by the study physician, physician assistant or nurse practitioner, who determines if conditions are present that meet exclusion criteria. Eligibility criteria are as follows:

**Gender** Men and women are eligible. The LIFE Study endeavors to recruit men and women in rough proportion to their representation in the catchment area population.

**Age** Individuals aged 70-<90 years old are eligible. This age group is selected because it is at high risk of major mobility disability, and it may have a sufficiently long life expectancy to participate in a full-scale RCT, which would have a duration of 3 to 4 years.

**Ethnicity** All ethnic groups are eligible for the study. The LIFE Study goal is for a study cohort that is at least 22.5% from minority populations (primarily African Americans and Hispanic Americans).

**Residency** Participants must be planning to reside in the area for at least 2 years.

**Functional Status** Summary score <10 on the Short Physical Performance Battery (SPPB). Ability to complete the 400 m walk test within 15 minutes without sitting or the help of another person, or the use of a walker. The LIFE Study goal is a target of 45% of randomized participants to have a score of < 8.

**Cognitive functioning** Persons are eligible if they do not report a diagnosis of dementia or score lower than our education-based cut-points on the Modified Mini-Mental State Exam (3MSE). Persons with 9 or more years of education who score <80 (<76 if African American) and those with less than 9 years of education who score <76 (<70 if African American or Spanish speaking) are excluded. Persons excluded because of low 3MSE scores will be advised by the research staff to take the results to his/her PCP for additional review since our testing is for research purposes only.

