#### 6.2.11. Cognition

Cognitive function is assessed at baseline (both computer battery and non-computer based battery) and at 18 (computer battery only), 24-months (non-computer based battery only), and at the PIV (non-computer based battery only) visits in all participants. Participants who are unable to take the battery components at 18 or 24 months will be allowed to take them at the 30 month visit. The LIFE Study cognition assessment battery measures were selected because they have been used often in research examining aging and cognitive disorders and have been improved by either cognitive or physical activity interventions. As described in Section 3.3, the DSST and the HVLT are the two cognitive measures upon which the cognition outcome in LIFE is powered and will be assessed in the following manner:

1. **Digit Symbol Substitution Test (DSST)** is a measure of attention and perceptual speed in which participants are given a series of numbered symbols and then asked to draw the appropriate symbols below a list of random numbers. The score is the number of correctly made matches in 2 minutes (120 seconds).
2. **The Hopkins Verbal Learning Test (HVLT)** is a 12-item list learning and memory test designed for brief, easy administration with proven participant tolerability in a variety of populations. The HVLT requires the participant to listen to a list of 12 words and repeat as many as possible. The task is repeated twice, for a total of three trials. Approximately 20 minutes later, s/he is asked to recall as many words as possible. The participant is also presented a yes/no delayed recognition trial consisting of a randomized list that includes the 12 target words and 12 non-target words, six of which are drawn from the same semantic categories as the targets. Scores for immediate recall (total of three trials), delayed recall, and recognition are calculated into a summary score.

In addition:

3. **The Modified Mini-Mental Status Exam (3MSE)** will be administered as a test of global cognitive function which assess a broad variety of cognitive measures. This is an expanded 100 point version of the original Folstein MMSE and has been used in large epidemiological studies and clinical trials to effectively screen for persons experiencing impaired cognition and estimate incident Mild Cognitive Impairment (MCI) or dementia (see below).

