Level of ADL disability will be repeatedly measured as a continuous, score variable. A comparison of average post-randomization levels of ADL disability between intervention groups will be performed using mixed-effects analysis of covariance techniques appropriate for repeatedly measured outcomes. These models will contain variables representing field center, gender, a follow-up time effect, the baseline level of ADL disability and an intervention effect. Initially, we will explore the appropriateness of a model containing random intercepts and slopes (for follow-up time). The appropriateness of a model containing a fixed effect for the intervention by follow-up time interaction will be evaluated.

**Secondary aim #7** will be to assess the cost-effectiveness of the intervention.

Cost-effectiveness analyses will be conducted following the guidelines of the Panel of Cost-Effectiveness in Health and Medicine. The ratio of direct costs of the physical activity intervention to the amount of quality-adjusted life years (QALYs) produced is calculated. Health care costs will be estimated and differences between the physical activity and lifestyle intervention groups will be calculated to examine whether any cost-offset may occur. LIFE takes a societal perspective. The trial uses the health education intervention as the comparator for all cost-effectiveness analyses. Results will be described as the incremental cost-effectiveness over the comparator. Sensitivity analyses will be conducted to examine whether the cost-effectiveness results change as a function of any estimates or assumptions made in the process. Decision modeling will be used to estimate long-term cost-effectiveness beyond the 1-year time horizon for which data collection is planned. Future health care costs will be discounted at a rate of 3% for any calculations or projections beyond the first year of follow-up.

**Tertiary aim #1** will be to explore the effects of the interventions on MCI/D.

Logistic regression will be used to assess whether the proportion of participants who convert to the composite outcome of MCI/D from baseline varies by intervention assignment. Baseline level of global cognitive function (3MSE score) will be used as a covariate in these analyses.

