**Tertiary Aim #5** will be assessed using a logistic regression model with adjustment for Field Center and gender for the outcome of dyspnea. Ventilatory capacity will be examined using two types of mixed model analysis of variance models. First, we will examine for different post-baseline mean levels of FVC and FEV1 using a model adjusting for the baseline level, time (categorical), Field Center, and gender. We will account for within-person correlation using a subject random effect. Second, we will examine for a difference in the rates of decline using a random intercept/random slope mixed model.

**Tertiary Aims #6 and 7** will be assessed using Cox proportional hazards models, stratified by Field Center and gender. Failure time is measured from the time of randomization to the occurrence of a pulmonary disorder (Aim 6) or combined cardiovascular event (Aim 7).

**Tertiary aim #8** will be to explore time by intervention interactions on the SPPB score and 400 m walk speed endpoints. Separate estimates of the intervention effect will be obtained for participants with different planned lengths of intervention. This will be achieved by introducing variables representing periods of randomization (i.e., groupings of consecutive months) into the repeated measures models for SPPB score and 400 m walking speed and exploring the interaction between these variables and the intervention effect. There may be some confounding between other factors and the month of randomization (e.g., staff familiarity with the intervention); however, this analysis could be important in determining how length of intervention may relate to efficacy. We also will use interaction terms like these to estimate intervention effects for 1-year epochs across follow-up to examine their consistency over time.

**Tertiary aim #9** will be to explore whether the relative effect of the PA intervention on measures of cognitive function varies according to baseline level of global cognitive function. Separate estimates of the intervention effect on measures of cognitive function will be obtained for participants grouped by baseline 3MS (<90 versus  $\geq 90$ ). Tests of interaction will be used to compare any differences between these groups.

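### Tertiary aim #9 tests whether the cognitive effect varies with baseline 3MSE only by cutting the score at 90, which discards about 30–50% of the interaction information if the effect is graded

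*Protocol*

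**What the plan says.** Section 12.2 of the Protocol sets out Tertiary aim #9 as an exploratory question: does the effect of physical activity on the cognitive measures depend on a participant's global cognition at baseline? The analysis follows in two sentences. First, "Separate estimates of the intervention effect on measures of cognitive function will be obtained for participants grouped by baseline 3MS", the groups being below 90 and 90 or above. Second, "Tests of interaction will be used to compare any differences between these groups". No interaction with the score as such is named.

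The 3MS of aim #9 is taken here to be the 3MSE of section 6.2.11, which says of it: "This is an expanded 100 point version of the original Folstein MMSE". Everyone has it at baseline. Tertiary aim #1 already uses it as a score: "Baseline level of global cognitive function (3MSE score) will be used as a covariate in these analyses".

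The other 3MSE thresholds in the protocol are 70, 76 and 80 for eligibility (4.1.2 and 4.2.1) and an upper bound of 88 for asking a proxy about daily functioning (6.2.11). No share of participants below 90, no interaction size and no power is stated for aim #9.

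**The concern.** The question is about a level, but the named test sees only which side of 90 a participant is on. A score of 89 is treated like every lower eligible score, and 90 like 100. If benefit rises or falls gradually with baseline cognition, the variation within each group carries information that the test does not use.

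Interaction tests usually have low power, so a real gradient becomes more likely to be missed. The answer also rests on one cut for which the document gives no reason. This is a method that the protocol fixes, both the form of the moderator and the test, rather than a detail that it leaves open.

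**Working it through.** **Inputs from the protocol.** 1,600 enrolled. Loss of 8% per year, so 0.92² = 84.6% observed at two years: 800 × 0.8464 = 677.1 per arm, 1,354 in all. Longitudinal correlation r = 0.50 to 0.70. Average effect 0.15 SD. Two-sided 0.05; section 3.3 describes "a covariate-adjusted z-test with Bonferroni critical value of 1.96".

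**Assumptions, not in the protocol.** The effect is linear in the 3MSE; the slope, per SD of 3MSE; the share below 90; and the shape of the 3MSE distribution.

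**Step 1: reproduce the plan's own figure.** The residual SD is √(1 − r²) = 0.866 at r = 0.50. The standard error of the arm difference is 2 × 0.866/√1,354 = 0.0471. Then 0.15/0.0471 = 3.19, and power is Φ(3.19 − 1.96) = 89.0%, against 89% in Table 3.3.2. All nine cells of that table reproduce within 0.5 points, so the model behind it is understood.

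**Step 2: the test on the score.** With 1:1 allocation and a standardized score, the interaction slope has the same standard error, 0.0471. A slope of 0.10 gives a noncentrality of 0.10/0.0471 = 2.12 and power of 56.5%.

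**Step 3: the cut.** For an interaction linear in the score, replacing the score by an indicator keeps a fraction R² of the information. R² is the squared correlation of score and indicator, and the noncentrality is multiplied by √R². For a normal score with share p below the cut, R² = φ(z_p)²/(p(1 − p)). At the median this is 0.3989²/0.25 = 0.637, and 2.12 × √0.637 = 1.70, so power is 39.6%.

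| Share below 90 | Information kept | Power at slope 0.10 (score: 56.5%) | Relative loss | Power where score has 80% | Relative loss |
|---|---|---|---|---|---|
| 50% | 63.7% | 39.6% | 30% | 60.8% | 24% |
| 30% | 57.6% | 36.4% | 36% | 56.6% | 29% |
| 20% | 49.0% | 31.8% | 44% | 50.0% | 37.5% |

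At a slope of 0.15 the score has 89.0% power, against 72.0%, 67.7% and 60.7% for the three splits.

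**Step 4: a more realistic score.** The 3MSE is capped at 100 and truncated at entry. Seven assumed skewed whole-number distributions, truncated at 76 or 80 and with 21–55% below 90, keep 63–70% of the information. The relative power loss is 25–31% where the score has 50% power and 19–24% where it has 80%.

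**Step 5: cross-check by simulation.** This used 1,000 trials per setting, 1,354 participants, correlation 0.5 and main effect 0.15. Power with the score, then with the cut at 30% / 50% below: slope 0.08, 40% against 26% / 27%; slope 0.10, 57% against 36% / 40%; slope 0.12, 75% against 48% / 52%. The formula and the simulation agree.

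**The case against.** The strongest case against acting has five parts.

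- **The size is not fixed by the document.** The split, the slope and linearity are all assumed. This stands, which is why a range is given.
- **The ranking of the two tests depends on shape.** If benefit steps at 90, the indicator is the right variable and the score is the diluted one, by the same R². This stands too. The protocol does not claim such a step, however, and its question is worded in terms of level.
- **The cut is not data-driven.** It is prespecified and, with whole-number scores, differs from the upper bound of 88 in section 6.2.11 by the single value 89. That is fair. Still, the protocol does not link the two, so the supportable statement is that no reason is given, not that none exists.
- **The aim is minor.** It is worded as exploration, is missing from the tertiary list in 12.1, and has no power claim. Primary and secondary tests are untouched. This limits the consequence.
- **A SAP that is not shown may add a model on the score.** It may, so the statement is only that this is the one moderator test that the protocol names.

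Two further inferences are not supported. A missed gradient would not have to be reported as a uniform effect, because separate estimates are promised whatever the test shows. Aim #1 also does not establish that the 3MSE enters as a continuous term: it says that the score is a covariate, without giving its form.

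**Conclusion.** The point holds. For a graded effect, the cut at 90 discards about 30–50% of the information on the interaction. This costs about 20–40% of power, relative to the score, where the score-based test has 50–80% power. The cases tried run from 19% to 44%. In the worked example power drops from about 57% to 36–40%.

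A reader might infer that the cut always costs a third or more of the power. The documents do not support that; it takes loss of information for loss of power. For a normal score cut at the median, 36% of the information goes, but the relative power loss never exceeds 31%, and it is 18% where the score has 90% power. None of the seven bounded, skewed scores lost a third of power. A loss that large needs an uneven split, about 30/70 or worse for a normal score, together with low to moderate power. The protocol does not say how many participants fall below 90.

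The conclusion rests on an interaction roughly linear in the score. Because the aim is exploratory, this is a worthwhile refinement and does not threaten the trial's conclusions.

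**What to change.** In Tertiary aim #9, make the interaction of intervention with the baseline 3MSE score the test, in the ANCOVA for DSST, HVLT and the cognitive composite. Use a linear term, with a spline as a check on shape. Keep the prespecified estimates for below 90 and for 90 or above as a descriptive display, and give the reason for 90 if there is one.

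The cost is one sentence of analysis wording. No data, visits or participants are added, and the planned subgroup estimates stay. The downside is the linearity assumption, which the spline examines and the two group estimates help to illustrate. The change does not make the test strong: at a slope of 0.10 the score-based version still has only about 57% power, so a null result should not be read as evidence of a uniform effect.

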### 13. Trial Organization

Several centers, cores and committees support key components of the study and ensure its successful conduct and completion (Figure 13.1.).

**Figure d.13.1. Study organization scheme**

[figure not shown]

The **Steering Committee**, which is charged with the overall governance of study conduct, consists of selected investigators of the Field Centers and other support Centers, and the NIA Project Officers. The Steering Committee approves the final protocols and manuals of operations, supervises the overall execution of the trial, generates and approves study policies, considers modifications of the protocol and study operations, plans and drafts study-related publications, and plans the protocol for the full-scale study. The Steering Committee appoints and charges the subcommittees described below. All major scientific decisions are determined by majority vote of the Steering Committee.

The **Executive Committee** includes the Co-chairs of the Steering Committee, the NIA project officer and two rotating members selected among Field Center PIs and the DMAQC PI. The Executive Committee functions as the main liaison between the study investigators and the NIA, is responsible for negotiating budgets, the fiscal management of the trial, allocating resources based on pre-set budgets and on performance of individual Field and Support Centers, and evaluating and reporting on progress, timeline benchmarks and deliverables.

The **Administrative Coordinating Center** performs the following tasks:

- Development and monitoring of subcontracts with all sites, matching timelines and deliverables
- Coordination of meetings and conference calls for Committees and Sub-Committees:
- Development of the Manual of Operations (MOP), protocol and intervention materials
- Update the MOP, protocol and intervention materials
- Development of the questionnaires and forms jointly with the DMAQC Center and with relevant sub-committees of the Steering Committee (see below)
- Development of study recruitment materials, jointly with a Centralized Media Group
- Development of systems for communication among Steering Committee and sub-committee members
- Mailing of materials to the Field Centers
- Tracking of equipment and supplies
- Coordination of training and certification of Field Center staff.

The **Data Management, Analysis and Quality Control Center (DMAQC)** performs the following tasks:

- Development of sample size and statistical analysis plans, including stopping guidelines
- Development of the centralized web-based data management system
- Development and maintenance of the study wide web-based tracking and monitoring system
- Development of the decentralized participant tracking system
- Development of the randomization protocol and procedures
- Development of systems for obtaining data from the ECG reading center
- Generating data quality reports for study sites, Steering Committee and DSMB meetings
- Participating in presentation of blinded and unblinded data to the DSMB
- Monitoring of adverse events
- Monitoring of all QC aspects of data collection, including measurement and intervention reliability
- Reviewing of proposed ancillary study protocols
- Participation in writing teams for manuscripts

- Generating tables of results and performing analyses for manuscripts
- Establishing procedures for ensuring safety and confidentiality of records to meet HIPAA guidelines
- Establishing procedures for archiving and backup of data
- Participation in meetings and calls for all committees

The **Lifestyle Resource Core** serves as the primary group responsible for monitoring the fidelity and quality control of the intervention, training and certifying all project intervention staff involved in the intervention protocols and in operation of the computerized tracking system, and assisting interventionists with problem solving and related adherence strategies throughout the course of the intervention. The team reviews tracking system reports, operates e-mail and phone-based contact systems for assistance with the intervention protocol and provides advice on dealing with problems that arise in delivering the intervention.

The **Biological Samples Committee** coordinates and standardizes the collection, processing and short-term storage of blood samples across all Field Centers; and devises training and quality control procedures for the biological samples processing and storage at the Field Centers.

The **Field Centers** recruit study participants, administer the physical activity intervention and the health education control, ensure retention and adherence of study participants, perform all study related assessments (including complete tracking of outcomes during follow-up), and enter the data into the web-based data entry system. The Field Centers work with all other centers, cores and committees to ensure the accurate implementation of the study protocol and the successful conduct and completion of the trial. The Field Center investigators participate in the study committees and manuscript.

The **Publications and Presentations Committee (P&P)** (a) encourages production of high quality publications and presentations in a timely fashion, (b) encourages broad participation by the study investigators in publications and presentations, and (c) assures accurate maintenance of a database on study publications.

The **Emerging Science Committee** monitors the literature, scientific meetings and input received from colleagues on the cutting-edge science related to topics that are relevant to the project, and advises the Steering Committee on emerging scientific issues that may affect the conduct and future directions of the study. The Committee also reviews plans for ancillary study proposals, including those that involve utilization of biological samples.

The **Measurement and Event Adjudication Committee** refines the assessment protocols, and works closely with the DMAQC Center and the Field Centers to ensure the quality control procedures. The Committee refines and implements strategies for the outcomes tracking and adjudication. The **Cognition Sub-Committee** serves as the primary group responsible for the design and implementation of the cognitive function assessment aspects of the trial. This committee will also oversee training and quality assurance of the cognitive assessment aspects of the trial as well as the procedure for adjudicating the exploratory outcome of MCI/Dementia incidence in the LIFE Study. Scientific leadership for manuscripts that involve reporting of the impact of the LIFE interventions on cognitive function will also originate from this committee

The **Intervention and Operations Committee** finalizes and refines the intervention protocols, and works closely with the DMAQC Center and the Field Centers to ensure the QC procedures and training for the intervention. The Committee develops the Intervention Manual, refines and implements strategies to monitor compliance, and together with the Recruitment, Adherence and Retention Committee, refines and implements strategies to enhance adherence to the intervention.

The **Medical Safety Committee** reviews masked study data related to the overall safety of study participation, develops safety reports for the Data and Safety Monitoring Board, addresses IRB issues (related to participant safety) that may arise, reviews clinical practice-related issues and oversees the clinical safety of all study participants.

The **Recruitment, Adherence and Retention Committee** refines and optimizes protocols and strategies for recruitment, adherence and retention of study participants. The Committee oversees recruitment progress at all sites, intervenes in cases of under-recruitment, and reports recruitment progress to the Steering Committee. The Committee oversees retention efforts and investigates and intervenes when a site is having retention problems.

A **Data Safety Monitoring Board (DSMB)** monitors all aspects of the study, including those that require access to any blinded data.

